## Abstract

**Background:**

The prevalence of anxiety and depression disorders is surging worldwide, prompting a pressing demand for psychological interventions, especially in less severe cases. Responding to this need, the Italian government implemented the “Psychological Bonus” (PB) policy, allotting 25 million euros for mental health support. This policy entitles individuals to a minimum of four to twelve psychological sessions. In collaboration with the National Board of Italian Psychologists, our study assesses this policy’s effectiveness. Indeed, the PsyCARE study aims to examine the utilization of the Psychological Bonus, evaluate its impact on adult and adolescent participants’ psychological well-being through pre- and post-intervention assessments and six-month follow-up, and conduct a longitudinal cost-effectiveness analysis of this policy. A secondary aim is to investigate the influence of these interventions on transdiagnostic factors, including emotion regulation and epistemic trust.

**Methods:**

The study involves licensed psychotherapists and their patients, both adults and adolescents, benefiting from the Psychological Bonus. Data collection is underway and set to conclude in December 2023. Psychotherapists will provide diagnostic information and assess patient functioning. In addition, patients will be evaluated on mental health aspects such as clinical symptoms, emotion regulation, epistemic trust, and quality of life. We will employ linear mixed-effects models to analyze the outcomes, accounting for both fixed and random effects to capture the hierarchical structure of the data.

**Discussion:**

We anticipate the study’s findings will highlight reduced psychological distress and improved quality of life for participants and demonstrate the Psychological Bonus policy’s cost-effectiveness. The study will gather data on the role of specific versus nonspecific therapeutic factors in psychotherapy while adopting a patient-tailored approach to identify effective therapeutic elements and examine transdiagnostic factors. Overall, this study’s findings will guide future measures within the Italian healthcare system, fostering a psychological health culture and providing valuable insights to the broader public.

**Study registration:**

https://osf.io/6zk2j

## Introduction

### A global mental health emergency

A recent epidemiological study from 204 countries and territories highlighted approximately 53 million cases of major depressive disorder and 76 million cases of anxiety disorders directly linked to the pandemic. Notably, the younger population experienced the most significant increase, with women being twice as affected as men by these disorders [1].

In Italy, the Mental Health 2021 report published by the Italian Ministry of Health in 2022 stated that 778,737 individuals sought assistance from public specialist mental health services during 2021. Furthermore, nationwide data showed that 3.3% of emergency room admissions (n = 479,276) were related to psychiatric issues. Among individuals seeking assistance for mental health-related problems, 14.6% resulted in hospitalization, while 72.1% were managed at home. Thus, 7 out of 10 individuals seeking mental health services do not present with severe enough conditions to require hospitalization but require some form of psychological support, nonetheless. Moreover, 39.6% of all admissions are diagnosed with neurotic and somatoform syndromes [2]. Available data supports the evidence that the current public mental health system does not adequately address chronic cases, sub-clinical severity, or those that do not involve emergency management.

According to the 2022 Organisation for Economic Co-operation and Development (OECD) report titled “Health at a Glance: Europe,“ there was an increase in unmet needs for mental health care during and after the pandemic, with 23% of adults reporting such conditions in spring 2022, compared to 20% in spring 2021. While comprehensive data remains limited, national estimates indicate that the prevalence of depressive symptoms during the pandemic was approximately twice as high as pre-pandemic levels in numerous European countries [3]. Also, when looking at children and adolescents, recent estimates from the World Health Organization indicate that one in six individuals aged 10–19 have a mental disorder, with depression, anxiety, and behavioral disorders being the primary causes of distress [4]. Similar figures have been confirmed in Italian adolescents by a recent literature review by Deolmi & Pisani (2020) that emphasized the high prevalence of anxiety and depressive symptoms among young Italians attributed to the pandemic, social isolation, and parental stress [5].

In response to this situation, several European countries have implemented strategies to enhance mental health support, including establishing new information channels, expanding entitlements to mental health services, and increasing funding to improve the availability and accessibility of these services [3].

### The “Psychological Bonus”: a measure for the Italian population

Italy lacks a designated mental health budget for overall outpatient services. Recent evidence highlighted the benefits of measures such as an “Individual Health Budget” (resources allocated to meet specific health needs) to improve individuals’ mental health burden and promote a person-centered approach to mental health [6]. Nonetheless, available findings represent only a small population at a regional level.

However, in 2022, the Italian government introduced a new “Psychological Bonus” (PB) policy. This initiative allocated 10 million euros for mental health support, with an additional 15 million euros added in response to the numerous requests. The “Psychological Bonus” contributes to the costs of psychotherapy sessions to support people experiencing anxiety, depression, and psychological fragility due to the pandemic emergency, the consequent socio-economic crisis, and other psychological difficulties. Italian citizens residing in the country and with a yearly Equivalent Economic Situation Indicator (ISEE) equal to or below 50,000 Euros could apply for the funding [7].

The benefit is granted once for every applicant and must be used within 180 days after approval. If the application is approved, the contribution is awarded up to 50 Euros per psychotherapy session and distributed until the maximum allocated sum is reached. The given sum is up to 600 Euros for those with an ISEE lower than 15,000 Euros, up to 400 Euros for a beneficiary with an ISEE between 15,000 and 30,000, and up to 200 Euros for a beneficiary with an ISEE above 30,000 but not over 50,000 Euros.

Thus, the PB supports a minimum of four up to a maximum of twelve sessions, depending on the individual’s income. Furthermore, the benefit is available for new psychotherapies as well as for individuals that are already in treatment.

In December 2022, the number of funding requests reached 395,604. Nevertheless, funding constraints permitted the acceptance of only 10.52% of all applications, totaling 41,657. Once the applications were received, a ranking list was compiled, giving preference to individuals with lower incomes. Additionally, 27,280 psychotherapists willingly made their services available to the “Psychological Bonus” applicants.

To date, no data is available on its utilization and effectiveness.

Indeed, as anxiety and depression symptoms are prevalent in the general population, the PB is a first-time initiative. Thus it is crucial to explore to analyze the diagnostic characteristics of those who applied for this policy, both from the therapists’ and patients’ perspectives [8, 9].

### Efficacy and effectiveness of psychological interventions: a delicate balance

Evaluating the cost-effectiveness and tangible impact on individuals’ well-being is essential to justify government and institutions’ promotion and funding of psychological interventions.

*Efficacy* and *effectiveness* can be interpreted as extremes on a continuum in psychotherapy research [10]. Research on efficacy aims to evaluate a therapy under ideal and controlled conditions. This often includes randomized controlled trials (RCTs) carefully designed to minimize potential confounding variables. The study participants are systematically selected to meet specific inclusion and exclusion criteria, and the therapy is delivered in a standardized, controlled manner. Thus, the primary question in efficacy research is: “Does the therapy work in a controlled setting?“.

An exemplary case of research on *efficacy* is the Improving Access to Psychological Therapy (IAPT) project launched by the United Kingdom government in 2008 to address the need for psychological prevention and treatment measures [11]. With its focus on promoting mental health, IAPT offered evidence-based therapies for depression and anxiety disorders, including cognitive behavioral therapy and counseling, adhering to the National Institute for Health and Care Excellence (NICE) guidelines [12]. The IAPT model was built on three crucial features: a stepped care model, evidence-based and highly standardized treatments, and the consistent application of outcome monitoring. In addition, these services used a care model, which aimed to distribute scarce resources for psychological therapy by providing low- and high-intensity interventions, highlighting the importance of investigating the effectiveness of psychological interventions. As a result, people received support promptly, using the least intrusive intervention first [11, 13].

A decade later, there are more than 200 IAPT services throughout England, making it the world’s largest publicly funded and systematic implementation of evidence-based psychological care. Indeed, it was the world’s largest publicly funded psychological therapy initiative, as a meta-analysis conducted by Wakefield et al. (2021) showed, fostering a substantial decrease in depression and anxiety symptoms among patients post-treatment and a medium increase in their work and social adjustment [14]. The success of the IAPT model has led other countries, including Australia, Canada, Norway, and Japan, to develop similar systems [15–18]. The IAPT model holds promise for global adoption and evolution to meet populations’ diverse and expanding mental health needs worldwide, providing a virtuous example of how evidence-informed programs can reshape public psychological care [19].

An *efficacy* study, like the one promoted by the IAPT model, aims at assessing and providing the maximal therapeutic effect that treatment can achieve. However, when put into practice, limitations rooted in the complexities of the clinical practice itself might occur. For example, participants may not have the full range of comorbid conditions commonly seen in real-world settings, and the therapists might not be sufficiently trained or strictly supervised in their adherence to a model in most community settings [20–22].

To overcome these limitations, we can consider research on *effectiveness* on the other side of the continuum from research on *efficacy*. Indeed, *effectiveness* research aims to evaluate how therapy works in real-world conditions, measure the degree of its beneficial effects in “real-world” clinical settings, and consider the overall value of treatment as it would be applied in routine clinical practice. Participants in these studies represent a broader patient population, and the therapy is delivered more flexibly, which might better reflect typical clinical practice. *Effectiveness* research often considers a broader range of outcomes, including quality of life, function, and patient satisfaction, not just symptom reduction. Indeed, the primary question addressed in effectiveness research is: “Does the therapy work in everyday practice?“.

Indeed, literature has pointed out that, although a systematic approach allows for a clearer understanding of both the study of the process (“how does it work?“) and outcome (“does it work for…?“) of psychotherapy, also encountering the reality of clinical practice is crucial.

### Beyond Symptomatology: transdiagnostic factors

Recent literature has highlighted the utility of considering transdiagnostic factors in psychotherapy. Indeed, they refer to the underlying causes of mental health problems that might share commonalities amongst different symptomatic phenotypes and allow evaluation of the effectiveness of an intervention targeting factors such as emotion regulation and interpersonal functioning.

For example, emotion regulation is pivotal in mental health and well-being. A growing body of research suggests that deficits in emotion regulation are a critical transdiagnostic factor implicated in developing and maintaining various psychological disorders, notably anxiety and depression [23, 24]. Individuals with inadequate emotion regulation strategies often experience intense, prolonged negative affects and struggle to rebound from stressors, contributing to a heightened vulnerability to both anxiety and depressive symptoms. For instance, maladaptive emotion regulation strategies, such as emotional suppression, are frequently observed in these populations. These patterns of emotional dysregulation can result in a vicious cycle, where an inability to manage emotional responses effectively leads to increased psychological distress, further exacerbating difficulties with emotion regulation and perpetuating symptoms of anxiety and depression [25].

Emerging research suggests that deficits in epistemic trust (i.e., the capacity to trust the information others provide as reliable and personally relevant) may be another crucial transdiagnostic factor [26, 27]. Individuals with impaired epistemic trust often struggle with accepting and utilizing external guidance, hindering their ability to learn from therapeutic interventions, social feedback, or supportive interpersonal relationships. Furthermore, a decreased capacity for epistemic trust (i.e., epistemic mistrust) may also lead to an overreliance on internal, often negatively biased, interpretations of events and emotions, thereby perpetuating maladaptive cognitive processes and thought patterns [28–30]. As such, literature highlighted the importance of understanding the role of epistemic trust within the broader context of psychopathology and the therapeutic process.

## Aims and hypotheses

The “Assessing Impact, Cost-Effectiveness, and Transdiagnostic Factors of the Italian Ministry of Health’s “Psychological Bonus” Policy” study (PsyCARE) is anchored in this scenario.

Thus, the primary outcomes of the 36-month-long study entail: [1] exploring the access to the PB by analyzing the demographic characteristics of adhering therapists and users; [2] assessing the impact of interventions on the psychological well-being of users (adults and adolescents) investigating differences on indicators of psychological well-being between a baseline measurement (T0), a post-treatment measurement (T1) and a 6-months follow-up measurement (T2); [3] assessing the economical impact of the PB conducting a cost-effectiveness analysis that considers the benefits in terms of improved psychological well-being of users between a baseline measurement (T0) and a post-treatment measurement (T1), considering both direct health care costs (cost of treatment) and indirect costs (loss of user productivity).

Finally, a secondary outcome of the study is exploring the impact of psychological interventions on emotion regulation and epistemic trust [23, 24, 26, 27].

Thus, four main hypotheses will be tested in line with the available literature.

First, both the therapists participating in the study, beyond their theoretical frameworks, and patients will report mainly anxious and depressive symptoms [8, 9].

Second, the longitudinal trajectories for all psychological well-being indicators will improve between a baseline measurement (T0), a post-treatment measurement (T1), and a follow-up measurement (T2). More specifically, we expect psychological distress, anxiety, and depression symptoms to improve after treatment for adult and adolescent patients and to remain stable at a six-month follow-up [14].

Third, the PB will be a cost-effective initiative in terms of improved psychological well-being of users (adults and adolescents) between a baseline measurement (T0) and a post-treatment measurement (T1), accounting for direct healthcare costs (cost of treatment) and indirect costs (loss of user productivity). Thus, we expect the intervention will improve participants’ quality of life and productivity (i.e., loss of days of school/work because of ill health).

Fourth, emotion regulation, epistemic mistrust, and epistemic credulity will improve between a baseline measurement (T0), a post-treatment measurement (T1), and a follow-up measurement (T2). Moreover, we expect emotion regulation and epistemic trust to impact the longitudinal trajectories of psychological symptoms.

## Methods

### Study design

The PsyCARE study includes observational studies that are both cross-sectional and longitudinal. The University of Milan-Bicocca coordinates the study in collaboration with the University of Bergamo, the University of Catania, the University of Palermo, the University “La Sapienza” of Rome, and the National Board of Italian Psychologists.

The research study strictly adheres to the ethical guidelines outlined by the American Psychological Association (APA) and the principles outlined in the Declaration of Helsinki (seventh revision, 2013). The Ethical Committee of the University of Milan-Bicocca approved all materials and procedures.

### Sampling plan

Data collection will include two samples. The first sample will consist of therapists registered with the National Board of Italian Psychologists, adhering to the Italian Psychologist Bonus initiative. The second sample will consist of participating therapists’ patients encompassing adults over 18 years old and adolescents aged between 14 and 18 using the Psychologist Bonus.

Therapists are recruited via online newsletters and web news promoted by the National Board of Italian Psychologists. Patients are recruited via their therapists’ participating in the study.

Before participating in the study, all participants will provide informed consent. For under-age participants, informed consent will be obtained from adolescents and their parents/legal guardians. Participation is entirely voluntary. As an incentive for enrollment, therapists can participate in a training course on psychological assessment for free and obtain forty out of the fifty yearly professional mandatory training credits [31].

Each therapist is assigned a unique six-letter reference code (i.e., ABCDEF). To ensure patients’ matching, the therapist will assign their unique code and a number for every patient enrolled (i.e., ABCDEF-1 for patient number 1, ABCDEF-2 for patient number 2, etc.). All self-report questionnaires are completed via a secure web link to ensure anonymity on the Qualtrics platform.

Our target sample size, is a minimum of 450 therapists and 450 patients (adults and adolescents) to achieve sufficient power for the study.

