#### Adolescent patients assessment at T0

After collecting informed consent from both adolescents and their parents, patients aged between 14 and 18 will provide demographics, information on productivity (i.e., how many days at school did you lose because of your psychological problems?), and self-report on psychological distress behavioral problems, emotion regulation (ERQ), epistemic trust (ETMCQ), and quality of life.

The *Young Persons’ Clinical Outcomes in Routine Evaluation* (YP-CORE) [49] is a brief 10-item measure to explore psychological distress in adolescents. Items are inspired by the CORE-OM and explore general well-being, symptoms/problems, functioning, and risk for the self. The questions all focus on how the person has felt in the past week. Each question has five possible answers, ranging from 0 = “Not at all” to 4 = “Most or all of the time”. The total clinical score is the sum of all scores (range 0–4) ranging from zero to 40. For our study, we wil reference the Italian validation of the YP-CORE [50].

The *Youth Self Report* (YSR) [51] is a 112-item self-report measure that assesses general psychological and behavioral difficulties. The YSR is the most widely used scale for assessing behavioral problems in adolescence, supported by excellent psychometric properties [52] Each item is scored on a 3-point scale (0= “not true” to 2= “very or often true”). The measure yields a Total Problems score of general pathological functioning and two comprehensive subscales of Externalizing behavior problems and Internalizing problems. The Externalizing scale encompasses the subscales of Aggressive behaviors and Rule-breaking behaviors. The Internalizing scale includes the Anxious/Depressed, Withdrawn/Depressed, and Somatic Complaints subscales. For this study, we will utilize the Externalizing and Internalizing problems scales and the Thoughts problems scale (e.g., strange behaviors, hallucinatory experiences, sleeping less). Higher scores indicate higher problems in the specific dimension.

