## Data analyses

​​Statistical analyses will be conducted using R Core Team ver. 4.3.1 [57].

We will compute descriptive statistics for all study objectives, utilizing the *psych* package [58], to examine the participants’ general characteristics.

We will compute descriptive statistics to explore access to the PB by analyzing the demographic characteristics of adhering therapists and patients (Objective 1). This will allow us to examine the characteristics of participants in terms of age, gender, socioeconomic status, and geographical location, among other pertinent variables (i.e., therapists’ expertise and theoretical framework; patients’ diagnostic information and severity of psychological distress).

To assess the impact of interventions on the psychological well-being of users (Objective 2), we will employ mixed models with random coefficients across participants using the R package *lme4* [59].

We conducted a power analysis using a simulation-based approach to estimate the minimum sample size required to detect a small effect size. The simulations were conducted using the R package *simr* [60]. The data simulation model was configured with random intercepts for participants. We assumed that all random variances were equal to 1, and the effect size of the outcome (slope) was computed to correspond to a Cohen’s d of 0.20 [61]. The correct slope coefficient value was calculated using the formulas described in Judd, Westfall, and Kenny [62]. Setting the simulations model with coefficients for the target effect random across participants ensures a pessimistic, and therefore more conservative, estimation of the minimum number of participants required [63]. According to the design, we varied the number of participants until the simulations showed the required power (1 − β = 0.80). The results of the power analysis indicated that a sample of N = 220 participants would provide a power of 0.80, and a sample of N = 290 would yield a power of 0.90. Accounting for a 50% dropout rate, we will to collect a minimum of 435 participants.

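### The 450-patient target is pooled over two age groups that complete different symptom scales, so at 50% dropout it cannot give 0.80 power for Objective 2 in both

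*Protocol article*

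**What the plan says.** **Target.** Sampling plan gives a single total: "a minimum of 450 therapists and 450 patients (adults and adolescents) to achieve sufficient power for the study". It does not say how many of the 450 should be adolescents.

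**Objective 2 power.** Data analyses reports a simulation in which "the effect size of the outcome (slope) was computed to correspond to a Cohen’s d of 0.20". From it, "a sample of N = 220 participants would provide a power of 0.80" and "a sample of N = 290 would yield a power of 0.90". It continues: "Accounting for a 50% dropout rate, we will to collect a minimum of 435 participants".

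**Other objectives.** Data analyses gives 199 pairs for the EQ-5D analysis (Objective 3). It gives 200 participants for 0.80 in the Objective 4 models. None of these figures is broken down by age.

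**Scales.** According to the T0, T1 and T2 assessment sections:
- adults only: CORE-10, GAD-7, PHQ-9, EQ-5D;
- adolescents only: YP-CORE, YSR, EQ-5D-Y;
- both groups: ERQ, ETMCQ and the therapist-rated GAF.

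**Hypothesis.** Aims and hypotheses makes the symptom claim for both groups: "we expect psychological distress, anxiety, and depression symptoms to improve after treatment for adult and adolescent patients and to remain stable at a six-month follow-up". On the YSR, the adolescent T0 section says "For this study, we will utilize the Externalizing and Internalizing problems scales and the Thoughts problems scale".

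**The concern.** A model of PHQ-9 or GAD-7 can only use adults, and a model of YSR can only use adolescents. CORE-10 and YP-CORE are likewise separate instruments unless a rule for combining them is written down, and the article states none. The sample available to each such model is therefore one age group, while the required 220 is set against a total that covers both.

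Objective 2 is one of the primary outcomes, and the Discussion says the results may inform future funding. If the general power statement is taken at face value, a non-significant adolescent result could be read as evidence of no benefit from an adequately powered analysis when its power for the planned effect was well below 0.80.

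**Working it through.** **Inputs.** From the article: 450 enrolled; 50% dropout; 220 for 0.80 and 290 for 0.90 (Objective 2); 200 for 0.80 (Objective 4); 199 pairs (Objective 3). Assumed: two-sided alpha of 0.05 for the mixed models, since 0.05 is stated only for the paired t-test, and a range of age splits, since none is given.

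**Step 1. The plan's own figures.**
- The paired t-test with d = 0.20, alpha 0.05 and power 0.80 gives 198.15, so 199. This is reproduced.
- The 220 cannot be reproduced exactly, because the time coding and slope variance of the simulation are not given in enough detail. A closed form with intercept, slope and residual variances of 1 and a slope of 0.2 × √3 gives 196 for 0.80 and 263 for 0.90. Other codings range from 33 to 589 for 0.80.
- I therefore calibrate to the stated 220: power(n) = Φ[(1.960 + 0.842) × √(n/220) − 1.960]. At n = 290 this gives 0.896 against the stated 0.90, so the plan's two figures agree with each other and the calibration is usable.

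**Step 2. Completers.** 450 × (1 − 0.5) = 225, five more than 220. At the stated minimum of 435 there are 217.5, and even the pooled power is 0.796.

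**Step 3. Break-even for adult scales, Objective 2.** 220 adult completers need 220/0.5 = 440 adults enrolled. That is 440/450 = 97.8%, leaving room for at most 450 − 440 = 10 adolescents.

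**Step 4. Both groups together.** 220 + 220 = 440 completers are needed and 225 are available, so no split gives 0.80 in both.

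**Step 5. Power under assumed splits (Objective 2, 50% dropout).**

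| Adults/adolescents | Adult completers | Adult power | Adolescent completers | Adolescent power |
|---|---|---|---|---|
| 90/10 | 202.5 | 0.77 | 22.5 | 0.14 |
| 80/20 | 180 | 0.72 | 45 | 0.24 |
| 70/30 | 157.5 | 0.66 | 67.5 | 0.34 |
| 50/50 | 112.5 | 0.52 | 112.5 | 0.52 |

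**Step 6. Other objectives, each against its own requirement.**
- Objective 4, adult symptom models: 200/0.5 = 400 adults, so 0.80 holds with up to 50 adolescents. At 90/10 the adult power is 0.81 and at 80/20 it is 0.76.
- Objective 3, adult EQ-5D: 199/225 = 88.4% of completers must be adults.
- GAF, ERQ and ETMCQ as outcomes can use all 225.

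**Step 7. Sensitivity to dropout.**
- With no dropout, 80/20 gives adults (n = 360) 0.95 and adolescents (n = 90) 0.43, and 50/50 gives 0.81 in each group (n = 225).
- At 80/20, adults keep 0.80 up to 1 − 220/360 = 38.9% dropout.
- The 435 equals 290 × 1.5, which corresponds to losing 145/435 = one third rather than one half. At that loss 450 leaves 300 completers. Adults then need 220/300 = 73.3% of them, and 440 for both groups is still out of reach.

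**The case against.** **Mixed models do not discard dropouts.** A patient lost after T0 or T1 still contributes data, so treating 225 as the whole sample understates power. Also, 450 is a minimum. This stands, and the table should be read as conservative. It does not remove the problem: even with no dropout at all, adolescents at 80/20 have 0.43.

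**CORE-10 and YP-CORE could be pooled.** Both have 10 items and are scored 0–40, and a combining rule could sit in an analysis plan that is not shown. That is fair for the distress outcome. It does not help GAD-7, PHQ-9 or YSR, which have no counterpart in the other group.

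**The effect assumed is small.** If d = 0.4 or 0.5 is assumed instead (neither is in the article), the same calibration gives 45 adolescent completers power of about 0.72 or 0.89. The low power therefore concerns small effects of the size the plan chose, and adolescent results would not be uninformative in general.

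**Two stronger readings are tempting.** A reader might infer that no symptom model has 0.80 power. The article does not support this, because the age split is unknown: adult Objective 2 models keep 0.80 with at most 10 adolescents enrolled, and adult Objective 4 models with at most 50. A reader might also infer that adolescent anxiety and depression are not measured. The adolescent T0 section says that Internalizing contains the Anxious/Depressed and Withdrawn/Depressed subscales alongside Somatic Complaints, so the construct is covered, though only within a composite.

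**Conclusion.** The point holds in limited form. The statement that 450 patients give sufficient power is not met for the age-specific symptom models of Objective 2 taken together: at the plan's 50% dropout, 225 completers cannot supply 220 in each group, whatever the split. Which models fall short, and by how much, depends on a split the article does not give. Adult models drop modestly (0.77 at 90/10, 0.72 at 80/20), while adolescent models are far below 0.80 at those splits (0.14 and 0.24).

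The figures rest on the stated 220 being correct, a two-sided alpha of 0.05, d = 0.20 and a completer-only count. The conclusion that both groups cannot reach 0.80 together also holds if the loss is one third. It would fail only with almost no attrition and a near-even split.

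**What to change.** In Sampling plan and Data analyses:
1. Replace the single pooled power statement with power per age group, for the expected adult/adolescent split, for every outcome measured on an age-specific scale. Use 220 for Objective 2, 199 pairs for the EQ-5D analysis and 200 for the Objective 4 symptom models as the respective benchmarks.
2. Keep the pooled figure only for measures both groups complete (GAF, ERQ, ETMCQ).
3. State that a non-significant adolescent result is not an adequately powered null, and report adolescent effects as estimates with 95% confidence intervals.
4. Optionally, also report the YSR Anxious/Depressed subscale for the adolescent anxiety and depression hypothesis. It is already collected within Internalizing.

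Naming adults as the confirmatory group, or setting recruitment targets per group, are possible choices, but neither is required. For scale, 0.80 in each group at 50% dropout would take 440 + 440 = 880 patients for Objective 2.

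The cost is wording and, if adopted, one extra subscale score. No extra patients are needed. The stated power becomes less favourable. The change is best made before the outcome data are analysed.
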